## Abstract

**Background overview and rationale:**

We co-developed a multi-component virtual care solution (TtLIVE) for the home mechanical ventilation (HMV) population using the aTouchAway™ platform (Aetonix). The TtLIVE intervention includes (1) virtual home visits; (2) customizable care plans; (3) clinical workflows that incorporate reminders, completion of symptom profiles, and tele-monitoring; and (4) digitally secure communication via messaging, audio, and video calls; (5) Resource library including print and audiovisual material.

**Objectives and brief methods:**

Our primary objective is to evaluate the TtLIVE intervention compared to a usual care control group using an eight-center, pragmatic, parallel-group single-blind (outcome assessors) randomized controlled trial. Eligible patients are children and adults newly transitioning to HMV in Ontario, Canada. Our target sample size is 440 participants (220 each arm). Our co-primary outcomes are a number of emergency department (ED) visits in the 12 months after randomization and change in family caregiver (FC) reported Pearlin Mastery Scale score from baseline to 12 months. Secondary outcomes also measured in the 12 months post randomization include healthcare utilization measured using a hybrid Ambulatory Home Care Record (AHCR-hybrid), FC burden using the Zarit Burden Interview, and health-related quality of life using the EQ-5D. In addition, we will conduct a cost-utility analysis over a 1-year time horizon and measure process outcomes including healthcare provider time using the Care Coordination Measurement Tool. We will use qualitative interviews in a subset of study participants to understand acceptability, barriers, and facilitators to the TtLIVE intervention. We will administer the Family Experiences with Care Coordination (FECC) to interview participants. We will use Poisson regression for a number of ED visits at 12 months. We will use linear regression for the Pearlin Mastery scale score at 12 months. We will adjust for the baseline score to estimate the effect of the intervention on the primary outcomes. Analysis of secondary outcomes will employ regression, causal, and linear mixed modeling. Primary analysis will follow intention-to-treat principles. We have Research Ethics Board approval from SickKids, Children’s Hospital Eastern Ontario, McMaster Children’s Hospital, Children’s Hospital-London Health Sciences, Sunnybrook Hospital, London Health Sciences, West Park Healthcare Centre, and Ottawa Hospital.

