### Sample size {14}

To determine our sample size we used simulations and data from our previous study of VAIs using Ontario health administrative data [2]. We simulated data based on a negative binomial distribution assuming 50% of VAIs visit the ED and had a mean number of 2.6 visits, for an overall yearly incidence rate of 1.3 ED visits. We need 200 participants/ study group to detect a 30% drop-in yearly incidence rate to of 0.91 at 12 months with *α* = 5% and power 80%. Given an estimated attrition rate of 10%, we will recruit a total of 440 participants. For our co-primary outcome, assuming a minimum clinically important difference in the Pearlin Mastery Scale score of 2.95, standard deviation of 4.5, power of 90%, and alpha = 5%, we would require a sample size of 50 study participants in each group for a total of 100 participants [38, 39]. Therefore, with our planned sample size of 440 participants, we are powered for our co-primary outcomes of ED visits and family caregiver reported Pearlin Mastery Scale score.

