## Statistical methods

### Statistical methods for primary and secondary outcomes {20a}

The number of ED visits will be analyzed using Poisson or negative binomial regression. Pearlin Mastery Scale scores at 12 months will be analyzed using linear or robust regression models depending on the distribution of the data and adjusting for baseline Pearlin score. Both analyses will adjust for the for the stratified clinical site. We will conduct a secondary analysis of the primary outcome, ED visits, adjusting for a priori chosen clinically important covariates: age, sex, and clinical site; and stratified by pediatric, adult ALS, and adult non-ALS and ventilation type (invasive or non-invasive ventilation). Analysis of secondary outcomes, viewed as exploratory in nature, will vary depending on the outcome: count data (i.e., number of hospitalizations) will be compared with Poisson or negative binomial regression as appropriate; hospital free survival via Kaplan- Meier curves and Cox proportional hazards; time to ED admission and hospitalization using Fine and Gray models to account for competing risk of death; continuous repeated measures outcomes (EQ-5D-3L/5D-Y, FECC, ZBI, and CCMT) using linear mixed effects models.

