### Methods in analysis to handle protocol non-adherence and any statistical methods to handle missing data {20c}

We will use intention to treat analyses as our primary analysis. We will also do a per-protocol analysis. We will describe the amount of missing data. Patterns of missing data will be visually inspected to determine the mechanism of the missing data associations between baseline variables. For the number of ED admissions, we will account for varying lengths of follow-up due to death using the follow-up duration as an offset in the Poisson or negative binomial model. Pearlin score will have a monotonic pattern of missing data and use inverse probability weighting to account for death and dropout. Depending on the amount of missing data for the secondary outcomes, sensitivity analysis will be performed to describe the impact of the missing data.

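### The abstract names Poisson regression for the co-primary ED-visit outcome and the methods leave Poisson or negative binomial open, although the trial was sized on negative binomial counts that are clearly overdispersed

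*Protocol article*

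**What the plan says.** The protocol article describes the ED-visit model in three places and the assumed distribution in a fourth.

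- **Abstract, Objectives and brief methods:** "We will use Poisson regression for a number of ED visits at 12 months". No alternative is given.
- **Statistical methods {20a}:** "The number of ED visits will be analyzed using Poisson or negative binomial regression", with adjustment for site. No criterion is attached to this choice. In the same paragraph the other count outcomes get whichever of the two models is appropriate, and the Pearlin model depends on how the data are distributed.
- **Missing data and non-adherence {20c}:** follow-up cut short by death is handled by "using the follow-up duration as an offset in the Poisson or negative binomial model".
- **Sample size {14}:** "We simulated data based on a negative binomial distribution assuming 50% of VAIs visit the ED", and they "had a mean number of 2.6 visits, for an overall yearly incidence rate of 1.3 ED visits". The target is "to detect a 30% drop-in yearly incidence rate to of 0.91 at 12 months", with alpha 5% and power 80%, and the result is "We need 200 participants/ study group".

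The article does not say which kind of standard error a Poisson model would use. The robust regression mentioned in {20a} is for the Pearlin score.

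**The concern.** A Poisson model takes the variance to equal the mean. The counts on which the trial was sized do not behave that way: a Poisson variable with mean 1.3 is zero with probability exp(−1.3) = 27%, whereas the design assumes 50%. A Poisson fit with the usual model-based standard errors would therefore give a confidence interval that is too narrow and reject a true null too often.

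ED visits are a co-primary outcome and the one that sets the sample size. The two permitted models can give intervals of materially different width from the same data, so which one is fitted could decide the conclusion. As published, the abstract, the methods and the sample size do not agree on one model.

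**Working it through.** **Inputs, all from Sample size {14}:** P(0) = 1 − 0.50 = 0.50; control mean 0.50 × 2.6 = 1.3; intervention mean 0.70 × 1.3 = 0.91; 200 per arm; alpha 5%, power 80%. Sidedness is not stated, so two-sided is assumed. No dispersion is stated and it has to be derived.

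**1. Dispersion from the literal inputs.** For a negative binomial with mean μ and shape k, P(0) = (1 + μ/k)^(−k). Setting (1 + 1.3/k)^(−k) = 0.5 gives k = 0.603, a dispersion 1/k of 1.66.
- Control arm: variance = 1.3 + 1.3² × 1.66 = 4.10, and variance/mean = 3.15.
- At the planned mean: variance/mean = 1 + 0.91 × 1.66 = 2.51.

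**2. The plan's own figure.** n per arm = (1.960 + 0.842)² × (1/1.3 + 1/0.91 + 2/k) / (ln 0.7)² = 7.849 × 5.183 / 0.1272 ≈ 320. Variants give 317 (pooled null variance), 305 (null at the control rate), 329 (difference scale) and 252 (one-sided). A pure Poisson calculation gives 115. None reproduces 200. Solving the same formula for n = 200 gives a dispersion of 0.69, hence variance/mean = 1 + 1.3 × 0.69 = 1.89. That value implies about 39% with no visit, not the stated 50%. The shortfall is a separate matter; here it means that the dispersion is uncertain and a range is needed.

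**3. Type I error of Poisson regression with model-based standard errors.** Under the null these standard errors are too small by √(variance/mean), so the nominal 5% test rejects with probability 2 × [1 − Φ(1.96 / √(variance/mean))].

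| Reading of the inputs | Variance/mean | Type I error |
|---|---|---|
| Negative binomial, P(0) = 0.5, mean 1.3 | 3.15 | 27% |
| Negative binomial, dispersion that gives 200 per arm | 1.89 | 15% |
| Half never visit, the rest 1 + Poisson(1.6) | 1.92 | 16% |
| Half never visit, the rest Poisson(2.6) | 2.30 | 20% |
| Half never visit, the rest truncated geometric | 2.90 | 25% |

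For the first row the standard error is too small by √3.15 = 1.78. Under the planned effect the factor is √(5.183/1.868) = 1.67, where 1.868 = 1/1.3 + 1/0.91.

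A limiting case: if everyone who visits had the same count, the variance would be 0.25 × 2.6² = 1.69, the ratio 1.3 and the error 8.6%. That is a floor and not a realistic case. It shows that half at zero with a mean of 2.6 among the rest is overdispersed whatever distribution is assumed.

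**4. Simulation under the first row, no treatment effect.** With 200,000 trials the Poisson test rejected in 26.7%, 27.0% and 26.8% at 198, 200 and 220 per arm. With 2,000 trials at 200 per arm the rates were:
- Poisson, model-based: 26.2%
- Poisson, robust: 5.0%
- quasi-Poisson: 4.9%
- negative binomial: 5.1%

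**The case against.** The strongest reply is that the authors plainly expected overdispersion. They simulated from a negative binomial and named that model as an option in both {20a} and {20c}. The abstract is a summary; it also shortens the Pearlin analysis to linear regression where {20a} says linear or robust. The natural reading of the methods is negative binomial if the data are overdispersed. That rule would work: in 2,000 simulated null trials at 200 per arm, a Pearson dispersion check flagged overdispersion every time, and switching to negative binomial gave a type I error of 5.4% (5.25% with dispersion 0.69). Much of this stands. But {20a} does not state that rule for ED visits, and the abstract still names a single model that conflicts with the design.

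Three stronger readings are tempting, and the article does not support them.

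- A reader might infer that the trial will run at a false-positive rate of about 26%. That needs Poisson to be chosen and model-based standard errors to be used. The methods commit to neither.
- A reader might infer that no robust variance is planned. The article is silent on it, but it is a condensed account and the statistical analysis plan is not at hand, so silence does not show absence.
- A reader might infer that the open choice invites picking the better p-value. Section {17a} says that the data analyst is blinded. This does not supply a rule, but it weakens that worry.

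Adjustment for site could also absorb some overdispersion, by an amount that the article does not allow one to estimate.

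**Conclusion.** The point holds in a limited form. The abstract's model for a co-primary outcome conflicts with the distribution on which the trial was sized, and the methods leave that model available without a stated criterion. If it were fitted with model-based standard errors, the type I error would be roughly 15% to 27% instead of 5%. The upper end takes the stated 50% and 1.3 literally; the lower end takes the dispersion that reproduces 200 per arm. Both assume a two-sided test, no true effect and no overdispersion absorbed by covariates. Because the methods already allow an adequate model, this should be fixed but is not critical.

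**What to change.** Name one primary model for ED visits, in the same words, in the abstract, {20a} and {20c}, before outcome data are analysed: negative binomial regression with a log link, log follow-up time as offset, and adjustment for site as already planned. Add that Poisson regression with sandwich standard errors will be used if this model does not converge. Naming that Poisson model as the primary one would be equally acceptable; negative binomial has the advantage of matching the sample-size section. Remove Poisson with model-based standard errors as a primary option. Applying the same rule to the other count outcomes would keep the section consistent.

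The change costs wording only, with no extra participants or data. The confidence interval will be wider than a model-based Poisson fit would give: by a factor of about 1.7 under the planned effect with the literal inputs, or about √((1.868 + 2 × 0.687)/1.868) = 1.3 with the milder dispersion. The narrower interval would not have had its stated coverage.

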**Discussion:**

This pragmatic randomized controlled single-blind trial will determine the effectiveness and cost-effectiveness of the TtLIVE virtual care solution compared to usual care while providing important data on patient and family experience, as well as process measures such as healthcare provider time to deliver the intervention.

**Trial registration:**

ClinicalTrials.gov NCT04180722. Registered on November 27, 2019.

## Administrative information

Note: the numbers in curly brackets in this protocol refer to SPIRIT checklist item numbers. The order of the items has been modified to group similar items (see http://www.equator-network.org/reporting-guidelines/spirit-2013-statement-defining-standard-protocol-items-for-clinical-trials/).

## Introduction

### Background and rationale {6a}

Ventilator-assisted individuals (VAIs) living at home represent a small yet rapidly growing population in Canada [1, 2], and indeed internationally [3, 4]. Canadian prevalence of VAIs is conservatively estimated at 12.9 per 100,000 population [5]. VAIs are among the highest cost users of healthcare resources: a 2018 cost analysis of Canadian adults using Home Mechanical Ventilation (HMV) identified a median (range) monthly cost per VAI of $5275 ($2291–$10,181) with 58% of costs derived from public funding and 39% associated with family caregiving time costs [6]. Beyond economic considerations, HMV places a significant physical, social, and psychological burden on patients and their family caregivers. Communication gaps between and among healthcare providers, patients, and their family caregivers are common. This impedes the prompt resolution of ventilation issues resulting in unnecessary emergent healthcare utilization and costs [7]. Furthermore, the loss of access to trusted healthcare providers following hospital discharge is experienced as service fragmentation [8, 9]. This often leads to the intensification of the family caregiver role. Caring for a VAI at home can negatively affect family caregiver health [10–12]. Infrastructure to support patients and family caregivers is paramount to ensure that VAIs can continue to remain at home, and with substantial cost savings for the public healthcare system.

Virtual care technology provides an opportunity to increase patient (and family) empowerment, enable patient- and family-centered care, facilitate knowledge sharing between healthcare providers and across healthcare sectors, and may eliminate the care silos and negative experiences of transitions across settings experienced by VAIs [13]*.* VAIs are an ideal population for virtual care technology for several reasons. First, clinical follow-up is challenging because of significant costs associated with specialized assistance for travel to healthcare appointments given VAI limited mobility, medical fragility, and reliance on medical technology. VAIs are at risk for adverse events during travel due to inability to maintain access to technology (e.g., pulmonary clearance regimens including timely inhalations and frequent suctioning). This is particularly worrisome as many Canadian VAIs have to travel upwards of 100 km to access the nearest specialist ventilation center [14]. Second, VAIs experience multiple care transitions between and within healthcare sectors as their health status and needs change. Formalized handover between providers is frequently lacking, resulting in information gaps and additional time spent by healthcare providers searching for care plan documentation. Third, VAIs experience a lack of timely access to respiratory health professionals for home follow-up, particularly in the early stages of home transition. International evidence suggests that virtual care has the potential to reduce VAI healthcare utilization and costs to the public health system [15–23].

To our knowledge, no previous study has rigorously evaluated the effectiveness of virtual care as a means of improving health service delivery during the transition to HMV for adults and children. Our *T*ransitions *t*o *L*ong-Term *I*n-Home *V*entilator *E*ngagement (TtLIVE) randomized controlled trial therefore seeks to inform the evidence base by evaluating a multi-component virtual care solution (TtLIVE) for the HMV population using the aTouchAway™ platform (Aetonix, Ottawa, Canada). The TtLIVE intervention enables virtual home visits; customizable care plans; basic clinical workflows that incorporate reminders, completion of symptom profiles and tele-monitoring; digitally secure communication via text messaging, audio and unscheduled video calls between patients, families, and healthcare providers as well as access to an education resource library for patients and families.

### Objectives {7}

We used the Quadruple Aim framework [24], developed by the Institute for Health Care Improvement, as our outcome framework. We focused our study outcomes on improvement in four core domains: (1) health, (2) patient and family experience, (3) health system cost, and (4) healthcare provider time and experience.

Our co-primary objective is to evaluate the effect of the TtLIVE intervention compared to standard of care on (1) emergency department (ED) presentation rates in the 12 months following newly transitioning to HMV and (2) family caregiver reported sense of mastery at 12 months [25].

Secondary objectives are to evaluate (1) number of hospital admissions and days in hospital within 6 and 12 months of newly transitioning to HMV; (2) hospital free survival at 6 and 12 months; (3) time to first ED visit and first hospital admission; (4) respiratory and non-respiratory mortality within 6 and 12 months; (5) number and type of outpatient specialist visits within 6 and 12 months; (6) number of family physician visits within 6 and 12 months; (7) homecare service use within 6 and 12 months; (8) incremental cost of the TtLIVE intervention per patient quality-adjusted life year (QALY) gained compared to usual care from both a health system and societal perspective at 12 months; (9) healthcare provider time using the Care Coordination Measurement Tool; (10) change in family caregiver burden Zarit Burden Interview score from baseline to 6 and 12 months; (11) change in VAI health-related quality of life (HrQoL) using the EQ-5D (adults) and ED-5DY (children) from baseline to 6 and 12 months; (12) change in patient reported Sense of Mastery using the Pearlin Self-Mastery Scale at 12 months; and (13) adverse events.

Process measures include a measure of the quality of care coordination using the Family Experiences of Care Coordination (FECC) measure and through qualitative interviews, as well as fidelity metrics of use of the virtual intervention by patients/families and health care providers.

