### Eligibility criteria {10}

Inclusion and exclusion criteria for the trial are detailed in Tables 1 and 2.

**Table 1 Tab1:** Inclusion and exclusion criteria for study participants

Inclusion	Exclusion
• Newly initiated (in-hospital or outpatient), defined as within 2 months, on a ventilator for HMV prescribed by a participating clinic	• Projected life expectancy of ≤ 2 months
• Reads, writes, and understands English. If patient does not meet this criterion, they have a caregiver that does	• Significant cognitive impairment and absence/inability of a family caregiver able to use aTouchAway™ or complete questionnaires on the subject’s behalf
• Provides informed consent	• Uncontrolled psychiatric illness
• Live in a non-institutionalized setting	• Enrolled in a research study to evaluate another eHealth platform or care coordination model of care
	• Plan to move outside of province in the next 12 months

**Table 2 Tab2:** Inclusion and exclusion criteria for family caregiver participants

Inclusion	Exclusion
• Primary caregiver of an individual newly initiated on HMV that consents to participation	N/A
• Reads, writes, and understands English	
• Provides informed consent	

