#### Intervention delivery

*Scheduled virtual clinic visits* will take place during the first week of trial enrolment and then at 3 months (±2 weeks), 6 months (±2 weeks), 9 months (±2 weeks), and 12 months (±2 weeks) depending on medical stability. Visit frequency aligns with usual care in-person or virtual visits.

A virtual care plan will be completed in partnership with the participant, caregiver, and health care team. This will include a summary of medical diagnoses, medications, allergies, ventilator and cough assist settings, and alarms as well as special precautions. The healthcare providers that are within the circle of care for the participant, will be given permission to access their “virtual chart.” In addition, during the first visit, a *virtual action plan* will be developed by the HMV team in partnership with the participant and caregiver to address clinical and/or ventilator-related concerns. This care plan will include triggers for plan activation and actions in the event of respiratory infection/deterioration and ventilator alarm issues. A pre-determined calling tree is embedded to enable timely and appropriate response from the appropriate responder for medical and ventilator concerns.

*Routine monitoring* of clinical symptoms, ventilator usage, and other equipment-related issues will be conducted through participant bimonthly (VentSS) and monthly (S^3^-NIV) questionnaires administered and answered over the aTouchAway™ platform. We have selected the S^3^-NIV questionnaire, developed for telemonitoring of patients using NIV [25], as our monthly questionnaire. We have included an adapted version for the study participants using invasive ventilation.

*As needed scheduled clinical consultations* can be requested by the VAI, caregiver, and/or healthcare providers in the event of (1) abnormal parameters detected from routine data monitoring (i.e., questionnaire responses yield yellow or red notifications to the healthcare team); and (2) requests made by the VAI or caregiver. We have programmed questionnaire responses within the aTouchaway platform so that one response of concern results in a yellow notification and > 1 results in a red notification.

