### Outcomes {12}

See Table 4 for a list of study outcomes.

**Table 4 Tab4:** Study outcomes and study measures/instruments

Study outcomes	Measure/instrument
Co-primary outcomes	
ED visit rates at 12 months	Health administrative data and AHCR-hybrid
Change in family caregiver reported sense of mastery at 12 months	Pearlin Self-Mastery Scale score
Secondary outcomes	
Healthcare utilization outcomes	
Number of hospital admissions and days in hospital over 6 and 12 months	Health administrative data and AHCR-hybrid
Hospital free survival at 6 and 12 months	Health administrative data and AHCR-hybrid
Time to first ED visit and first hospital admission	Health administrative data and AHCR-hybrid
Overall survival at 6 and 12 months	Health administrative data and AHCR-hybrid
Number and type of outpatient specialist visits at 6 and 12 months	Health administrative data and AHCR-hybrid
Number of family physician visits at 6 and 12 months	Health administrative data and AHCR-hybrid
Homecare service use at 6 and 12 months	Health administrative data and AHCR-hybrid
Participant and caregiver outcomes	
Change in caregiver burden from baseline to 6 and 12 months	Zarit Burden Interview
Change in VAI health-related quality of life (HrQoL) from baseline to 6 and 12 months	EQ-5D-5L (adults) and EQ-5DY (children)
Change in patient reported sense of mastery at 12 months	Pearlin Self-Mastery Scale score
Ventilator use/alarms and signs and symptoms questionnaire	VentSS and the S^3^-NIV questionnaires
Economic outcomes	
Cost utility (ICER) of TtLIVE intervention compared to usual care in improving patient utility	AHCR-hybrid; provincial datasets (IC/ES); provincial costing sources (OCCI); EQ-5D-5L (adults) and EQ-5DY (children)
Healthcare provider outcomes	
Healthcare provider time	Care Coordination Measurement Tool
Process measure outcomes	
Quality of care coordination	Family Experiences of Care Coordination
Adherence to TtLIVE intervention by VAIs/family caregivers over 12 months and platform usage	aTouchAway Metrics
Adherence to TtLIVE intervention by healthcare providers over 12 months and platform usage	aTouchAway Metrics
Adverse events	
Adverse events unique to the use of the aTouchAway™ platform and the internet (technical issues due to software (aTouchAway™ platform) or hardware (the iPad/ phone/ computer being used) failure, privacy, and security breach	Direct reporting from Aetonix, patient, and caregiver

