### Consent or assent {26a}

Potential participants will be introduced to the study by a physician or clinic team member from the participating sites during a clinic appointment, hospital admission, or other patient encounters when HMV prescription occurs. The physician/HMV team member will review the study participant information sheet with the individual and family member. Interested and eligible individuals will be contacted by the unblinded research coordinator (MA) via email or telephone within 0–2 months of HMV initiation to obtain written informed consent.

{26b}

Additional consents for biological specimens are not necessary.

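### The Objectives start the ED co-primary window at transition to HMV, the abstract starts it at randomisation, and no other section names the start date

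*Protocol article*

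**What the plan says.** The protocol article gives two starting points for the same outcome.

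- **Objectives {7}:** the ED co-primary is "emergency department (ED) presentation rates in the 12 months following newly transitioning to HMV". A secondary objective uses the same origin: "number of hospital admissions and days in hospital within 6 and 12 months of newly transitioning to HMV".
- **Abstract, Objectives and brief methods:** the ED co-primary is the "number of emergency department (ED) visits in the 12 months after randomization". The abstract then says that the secondary outcomes, among them healthcare utilisation, are also measured over the 12 months post randomisation.

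Three sections bear on how far apart the two origins can lie.

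- **Eligibility criteria {10}, Table 1:** "Newly initiated (in-hospital or outpatient), defined as within 2 months, on a ventilator for HMV prescribed by a participating clinic".
- **Consent or assent {26a}:** the coordinator contacts interested patients "within 0–2 months of HMV initiation to obtain written informed consent".
- **Intervention delivery:** the scheduled virtual visits begin after entry; the first "will take place during the first week of trial enrolment".

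The remaining places do not settle the matter. Table 4 under Outcomes {12} has only "ED visit rates at 12 months". The Health administrative data section refers to the trial's 12-month period without saying when it begins. Section {20c} uses follow-up duration as the offset in the ED model, again without a start date.

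**The concern.** A comparison of randomised groups should count events from the point at which the groups were formed. Time between HMV initiation and randomisation belongs to neither treatment: no one has TtLIVE yet, and visits in it are expected equally in both arms. Counting that time has two effects. It adds events that allocation cannot change, and because the window is fixed at 12 months, it removes the same length of follow-up from the end, when the intervention arm is still being treated. Both pull the rate ratio towards 1.

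The choice matters in practice because ED visits and admissions come from linked provincial administrative data. Such data can be extracted from either date with equal ease, so the index date that is programmed decides which outcome is analysed. The conflicting wording sits in the formal Objectives and concerns a co-primary outcome.

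**Working it through.** **Inputs**

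- Control rate 1.3 ED visits a year, target 0.91, 200 per group, 5% alpha, 80% power: Sample size {14}. Sidedness is not stated; two-sided is assumed.
- Maximum lag from HMV initiation to enrolment, 2 months: Table 1 and Consent or assent {26a}.
- Average lag: not given. One month is used as an assumption; it is the mean if lags are spread evenly over 0 to 2 months.
- Constant ED rate over time: an assumption.

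**The plan's own figures**

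0.5 × 2.6 = 1.3 and 1.3 × 0.70 = 0.91, so the design rate ratio is 0.70. A negative binomial Wald calculation,

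n = (z_α + z_β)² × [(1/m1 + k) + (1/m2 + k)] / (ln RR)²,

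with dispersion k = 1.66 (solved from 50% with no visit at a mean of 1.3) gives 320 per group, not 200. The plan's simulation settings are not stated, and k = 0.69 returns 200. That is a separate question. Here the stated 80% is taken as nominal.

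**Dilution of the rate ratio**

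With d months of the 12 falling before randomisation,

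RR_obs = [d + (12 − d) × 0.70] / 12 = 0.70 + 0.30 × d/12.

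This is linear in d, so at a constant rate only the average lag matters.

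- d = 1: (1 + 11 × 0.70)/12 = 8.7/12 = 0.725
- d = 2: (2 + 10 × 0.70)/12 = 9.0/12 = 0.75

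**Power, scaling from the nominal 80%**

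Power = Φ(|ln RR_obs| / |ln 0.70| × 2.80 − 1.96).

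- d = 1: 0.3216/0.3567 = 0.902; 0.902 × 2.80 − 1.96 = 0.57; power about 71%
- d = 2: 0.2877/0.3567 = 0.807; 0.807 × 2.80 − 1.96 = 0.30; power about 62%

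**Check with the negative binomial formula, k = 0.69**

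| Average lag | RR_obs | Power at 200 per group | n per group for 80% |
|---|---|---|---|
| 0 | 0.70 | 80% | 200 |
| 1 month | 0.725 | 72% | 243 |
| 2 months | 0.75 | 63% | 300 |

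The two routes agree to within one percentage point.

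**Six-month windows**

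The same lag takes up twice the share. If a true ratio of 0.70 also applied to the 6-month admission outcome (illustrative; the plan gives no such effect), it would become (1 + 5 × 0.70)/6 = 0.75 at 1 month and (2 + 4 × 0.70)/6 = 0.80 at 2 months.

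**The case against.** The strongest reply is that the article as a whole points to a trial clock. The abstract names randomisation for the co-primary and again for healthcare utilisation. The administrative data section, the post-trial care section and the cost-utility section all speak of the trial or study period. The AHCR-hybrid, the second source of ED visits, is collected at baseline and every 4 weeks after that. Follow-up duration in a randomised trial ordinarily begins at randomisation. The article also uses newly transitioning as its standing label for the population, so the Objectives may just be loosely worded. This stands as evidence of probable intent. It does not remove the contradiction, because outside the abstract none of these places states a start date.

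A second reply is that transition need not mean initiation. The 2-month limit runs from initiation, which may take place in hospital; the move home can come later and so closer to enrolment. This also stands. Two months is an upper limit under one reading of the word, and the typical gap is unknown.

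A reader might go further than the documents allow in three ways.

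- **That the trial has chosen a window reaching back before randomisation, or will have 62% power.** No section sets out such an analysis. The 62% needs the Objectives' window and a full 2-month lag in every patient.
- **That ED use peaks around initiation, so dilution would be worse.** The article gives no ED rates by time since initiation. The Introduction's remark about poor early access to respiratory professionals concerns access, not ED visits, and patients started in hospital could have fewer visits at first.
- **That having to survive until randomisation biases the comparison.** That condition applies equally to both arms and favours neither.

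**Conclusion.** The two definitions contradict each other, and the article does not resolve them. The consequence is conditional. If the abstract's definition is used, nothing is lost. If the Objectives' definition is used, with transition read as HMV initiation and a constant ED rate, a true ratio of 0.70 is seen as 0.725 at an assumed average lag of 1 month (power about 71%) and as 0.75 at the extreme of 2 months for everyone (about 62%). The bias is towards no effect, so the risk is a missed benefit rather than a false one. The hospital-admission and hospital-days objectives share the problem, more sharply at 6 months. The mortality objective does not: it names no origin at all, so only consistency calls for adding one.

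This is an inconsistency in an outcome definition that should be fixed before data linkage. The full protocol, any analysis plan and the dataset creation plan are not shown and may already fix the date.

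**What to change.** - Reword Objectives {7} so that the ED co-primary and the 6- and 12-month utilisation outcomes, including admissions and days in hospital, are counted from the date of randomisation. State the same origin in Table 4.
- In section {20c}, say that the follow-up duration used as the offset starts on that date.
- Use the date of randomisation as the index date for the administrative data linkage, and confirm that the dataset creation plan agrees.
- State the same origin for mortality, for consistency.

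The cost is a few words and one index-date variable. No new data are needed, and the sample size and conduct of the trial are unaffected.
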